## Abstract

**Background:**

Parkinson's disease (PD) is a progressive neurodegenerative disorder for which no curative therapy currently exists. Qihuang needle therapy (QNT) is a novel acupuncture technique that has demonstrated clinical promise in alleviating PD symptoms, but its neuroplasticity mechanisms remain unexplored. This trial aims to investigate the efficacy and neurological effects of the QNT via multimodal MRI.

**Methods:**

This triple-arm randomized controlled trial will enroll 69 PD patients randomized into three groups (1:1:1): verum acupuncture, sham acupuncture, or wait-list control. Patients in the verum and sham groups will receive eight treatment sessions over 4 weeks, followed by an 8-week follow-up period. The control group will not receive any acupuncture treatment throughout the trial. Clinical outcomes included the Unified Parkinson's Disease Rating Scale Part III (UPDRS-III), Non-Motor Symptoms Scale (NMSS), 39-item Parkinson's Disease Questionnaire (PDQ-39), muscle rigidity (shear-wave elastography), and gait/balance parameters (Footscan system). Multimodal MRI will evaluate neuroplasticity markers: gray matter volume, functional connectivity, white matter integrity, nigral iron deposition, and neuromelanin content.

**Discussion:**

This protocol pioneers the integration of the QNT with advanced neuroimaging to elucidate its neuroplasticity mechanisms in PD, providing high-level mechanistic evidence for the integration of the QNT into PD care and optimizing integrative treatment strategies that combine traditional Chinese and Western medicine.

**Clinical trial registration:**

(http://itmctr.ccebtcm.org.cn/), Identifier :ITMCTR2025000402.

## Introduction

1

Parkinson's disease (PD) is the second most prevalent neurodegenerative disorder worldwide, affecting nearly 12 million individuals globally, with its burden projected to rise steadily due to population aging (1). Clinically, PD manifests as resting tremor, rigidity, bradykinesia, and postural instability, underpinned by progressive nigrostriatal dopaminergic degeneration and α-synuclein pathology (2). Although levodopa remains the mainstay of pharmacotherapy, long-term use is limited by many complications and failure to halt disease progression (3). These limitations underscore the need for non-pharmacological approaches, including physical therapy, occupational therapy, and acupuncture, which are recommended by international guidelines to optimize comprehensive PD care (4, 5).

Acupuncture has gained recognition in international guidelines as a complementary therapy for PD (6). Among various techniques, Qihuang needle therapy (QNT) developed from classical *Huangdi Neijing* principles, is distinguished by its unique needle design and operational methodology. A randomized controlled trial showed that QNT significantly improves UPDRS-III scores, gait parameters, muscle rigidity, and non-motor symptoms (7). However, the neurobiological basis of these benefits, particularly the effects on brain network reorganization and neuroplasticity, remains unknown.

Neuroplasticity plays a dual role in PD: adaptive plasticity may initially mitigate symptoms, whereas maladaptive changes may accelerate degeneration (8, 9). Multimodal magnetic resonance imaging (MRI) enables non-invasive assessment of structural and functional brain alterations, providing insights into PD-related neuroplasticity (10). Acupuncture has been shown to modulate brain networks in other neurological conditions, such as improving white matter integrity after mild traumatic brain injury (11), reorganizing motor networks in stroke (12), and modulating key regions in mild cognitive impairment (13). However, despite these promising insights, systematic neuroimaging investigations specifically targeting Parkinson's disease remain scarce. However, no study has systematically applied multimodal MRI to investigate the neuromodulatory and neuroplastic effects of QNT in PD.

This study aims to: (1) conduct a triple-arm randomized controlled trial to evaluate the clinical efficacy of QNT in PD, and (2) integrate multimodal MRI to map functional connectivity reorganization, gray matter volume changes, white matter integrity, nigral iron deposition, and neuromelanin preservation, thereby identifying neuroplasticity targets induced by acupuncture.

## Methods

2

### Study design

2.1

This is a parallel, triple-arm, randomized, sham-controlled trial designed to evaluate the clinical efficacy of the QNT and elucidate its neuroplasticity mechanisms in PD. Eligible PD patients will be randomized into three groups (1:1:1): verum acupuncture, sham acupuncture, or wait-list control. The total observation period spans 9 weeks, including a 1-week baseline, a 4-week intervention, and a 4-week follow-up. Additionally, 20 age- and sex-matched healthy controls (HCs) will be recruited to provide normative reference data for baseline MRI comparisons. The HCs data will be used to establish PD-related brain alterations by comparing HCs vs. PD patients at baseline, thereby identifying disease-specific structural and functional abnormalities that may be modulated by QNT.

The protocol adheres to the Standard Protocol Items: recommendations for Intervention Trials (SPIRIT (14) (Supplementary material 1) and the Standards for Reporting Interventions in Clinical Trials of Acupuncture (STRICTA) (15). A flowchart of the study design is shown in Figure 1, and assessment time points are detailed in Table 1.

**Figure 1 F1:**
[figure not shown]
Trial flow chart. PD, Parkinson's disease; VA, Verum acupuncture; SA, sham acupuncture; HCs, healthy controls; MRI, magnetic resonance imaging; AE, adverse events; SAE, serious adverse events.

**Table 1 T1:** Time points of treatment assessment.

Time point	Enrollment	Baseline	Treatment		Follow-up
	Week 1	Week 0	Week 2	Week 4	Week 8
Screening and enrollment					
Clinical interview	×				
Laboratory test	×			×	
Eligibility screen	×				
Informed consent	×				
Randomization		×			
Interventions					
Acupuncture			Eight sessions treatment + basic treatment		
Sham acupuncture			Eight sessions treatment + basic treatment		
Waiting-list			Basic treatment		
Assessments					
UPDRS-III		×		×	×
MDS-NMSS		×		×	×
PDQ-39		×		×	×
Footscan		×		×	
Synapsys		×		×	
SWE		×		×	
Multimodal MRI		×		×	
Others					
AEs, SAEs			×	×	×
Blinding assessment			×^*^	×	
PESA		×			
Patient compliance				×	×
Deqi sensation assessment^**^			×	×	
Medication adherence		×	×	×	×

^*^Assessed after the first and fourth session of acupuncture treatment.

^**^Assessed immediately after each acupuncture treatment.

UPDRS-III, Parkinson's Disease Rating Scale part III motor examination; NNMS, Parkinson's Disease Non-motor Symptom Scale; PDQ-39, 39-item Parkinson's Disease Questionnaire; SWE, shear wave elastic imaging; MRI, magnetic resonance imaging; AE, adverse events; SAE, serious adverse events; PESA, patients expectation scale of acupuncture.

### Participants

2.2

#### Inclusion criteria for PD patients

2.2.1

(1) Diagnosis of idiopathic PD according to established diagnostic criteria (16) and no change in the type or dose of anti-parkinsonian medication for at least 4 weeks.(2) Age 25–80 years;(3) Hoehn-Yahr stages 1–4.(4) Patients with no contraindications to MRI or who were willing to undergo imaging.(5) Conscious, stable vital signs without severe cognitive or auditory impairments.(6) Signed informed consent.

#### Exclusion criteria for PD patients

2.2.2

(1) Secondary parkinsonism (e.g., vascular, drug-induced).(2) MRI contraindications (e.g., metal implants) or severe systemic diseases.(3) Participation in other clinical trials within the past 3 months.(4) Severe psychiatric disorders or communication barriers.

#### Inclusion criteria for HCs

2.2.3

(1) Age 25–80 years; no gender restrictions.(2) No history of PD, parkinsonian syndromes, or cardiovascular diseases.(3) No MRI contraindications.(4) Conscious, stable vital signs, without cognitive or auditory impairments.(5) Signed informed consent.

#### Exclusion criteria for HCs

2.2.4

(1) MRI contraindications (e.g., claustrophobia).(2) Presence of PD-related motor symptoms (e.g., tremor, rigidity).(3) Cardiovascular diseases (e.g., hypertension, stroke) or severe comorbidities (e.g., cancer, renal failure).(4) Psychiatric or communication disorders.

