#### Clinical data analysis

2.9.1

All statistical tests will be two-tailed, with significance set at α = 0.05. Baseline demographic and clinical characteristics will be summarized descriptively by group. Baseline demographic and clinical characteristics will be summarized descriptively by group. To assess baseline comparability among the three randomized groups, one-way ANOVA (or Kruskal–Wallis test) will be used for continuous variables, and chi-square tests for categorical variables. If significant between-group differences are observed at baseline, the affected variables will be included as covariates in subsequent analyses to adjust for potential confounding. For the primary clinical outcome, no correction for multiple comparisons is applied as this is a single predefined comparison. For secondary clinical outcomes, we will apply False Discovery Rate (FDR) correction within each assessment scale. Continuous data will be analyzed via one-way ANOVA (normally distributed data) or the Kruskal–Wallis *H*-test (non-normal data), with Bonferroni-adjusted *post-hoc* comparisons. Categorical variables will be analyzed using the Pearson χ^2^ test or Fisher's exact test for unordered variables, and the linear trend χ^2^ test for ordered variables. Analysis of covariance (ANCOVA) will be employed to adjust for baseline values, age, disease duration, and levodopa equivalent daily dose where appropriate. If significant baseline differences between groups are observed after randomization, these variables will be included as covariates in the corresponding models to mitigate bias. Missing data will be handled using multiple imputation by chained equations under the missing at random assumption, with sensitivity analyses comparing imputed results to complete-case analyses. An intention-to-treat (ITT) analysis will include all randomized participants, whereas per-protocol analyses will exclude non-compliant cases (< 80% session attendance).

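### Healthy controls are screened for any cardiovascular disease, including hypertension, and PD patients are not, so the baseline PD-HC contrast does not by itself show disease-specific abnormalities

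*Protocol article*

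**What the plan says.** Section 2.1 (Study design) says that "20 age- and sex-matched healthy controls (HCs) will be recruited to provide normative reference data for baseline MRI comparisons". It gives the purpose of comparing them with PD patients at baseline as "thereby identifying disease-specific structural and functional abnormalities that may be modulated by QNT".

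The two groups have separate eligibility lists.

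- **HCs.** Section 2.2.3 requires "No history of PD, parkinsonian syndromes, or cardiovascular diseases". Section 2.2.4 excludes "Cardiovascular diseases (e.g., hypertension, stroke) or severe comorbidities (e.g., cancer, renal failure". Only the comorbidity part carries a severity qualifier. The cardiovascular part has none.
- **PD patients.** Section 2.2.1 asks for "Conscious, stable vital signs without severe cognitive or auditory impairments". Section 2.2.2 excludes "Secondary parkinsonism (e.g., vascular, drug-induced" and "MRI contraindications (e.g., metal implants) or severe systemic diseases". Neither section mentions hypertension or cardiovascular disease.

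The covariates named in section 2.9.1 serve to "adjust for baseline values, age, disease duration, and levodopa equivalent daily dose where appropriate". None is vascular. Section 2.9.2 names no vascular covariate or restricted analysis for the PD-HC contrast, and refers to Supplementary material 3 for detail.

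**The concern.** A comparison with controls isolates the disease only if the groups are otherwise alike on what moves the markers. Here they differ by design in a second respect: controls have no vascular history, while patients aged up to 80 may have one. Matching on age and sex does not remove this, because the selection operates within age and sex.

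The markers compared are gray matter volume, functional connectivity, diffusion measures and nigral measures. The resting-state fMRI section itself describes the BOLD signal in terms of neurovascular uncoupling, so it is reasonable to allow that vascular disease could shift some of them. If it does, part of the PD-HC difference is vascular and would be reported as PD. A later statement that QNT modulates a PD abnormality could then refer to a region that stands out partly for another reason.

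**Working it through.** **1. Group sizes.** Section 2.3 starts from 20 per group and allows 10% attrition: 20 / 0.90 = 22.2, rounded up to 23, and 3 × 23 = 69 PD patients. The stated 69 reproduces. The contrast is 69 PD patients against 20 HCs.

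**2. Who is eligible.**

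| Condition | As HC (2.2.3, 2.2.4) | As PD patient (2.2.1, 2.2.2) |
|---|---|---|
| Hypertension, not severe | Excluded | Eligible |
| Other cardiovascular disease, not severe | Excluded | Eligible |
| Severe cardiovascular disease, major stroke | Excluded | Arguably excluded as severe systemic disease |
| Vascular parkinsonism | Excluded | Excluded |

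The clear gap is in the first two rows.

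**3. Size of the bias.** Let p be the proportion of PD patients with vascular disease (zero in HCs) and d the shift it causes in a marker, in SD units. With no true PD effect, the expected PD-HC difference is p × d. The document gives neither input, so both are assumptions: p from 0.20 to 0.50, d from 0.2 to 0.6.

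- Low end: 0.20 × 0.2 = 0.04 SD.
- High end: 0.50 × 0.6 = 0.30 SD.

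**4. Set against the precision of the contrast.** For an unadjusted two-sample comparison with SD 1, SE = √(1/20 + 1/69) = 0.254. The bias is then 0.04 / 0.254 = 0.16 to 0.30 / 0.254 = 1.18 standard errors.

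**5. Whether a vascular covariate helps.** Take y = a + b·PD + c·V, where V marks vascular history and is 0 for every HC. Three cells exist:

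- HC: mean a
- PD without vascular history: mean a + b
- PD with vascular history: mean a + b + c

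Three means identify three parameters. c is estimated within PD patients, and b is the mean of PD patients without vascular history minus the HC mean. That is the same contrast as restricting the PD group, with essentially the same standard error.

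**6. Price of the restriction.** With p = 0.20, 69 × 0.80 ≈ 55 patients remain. With p = 0.50, 69 × 0.50 ≈ 35 remain.

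- 55 retained: SE = √(1/20 + 1/55) = 0.261.
- 35 retained: SE = √(1/20 + 1/35) = 0.280.

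The loss is small because the 20 HCs contribute most of the variance.

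**The case against.** **The contrast is secondary.** Section 2.6.1 makes change in MRI biomarkers the primary endpoint. Section 2.9.2 takes its seeds from an atlas, names the bilateral putamen in advance as the primary seed, and fixes the diffusion and nigral regions anatomically. None of these depends on the PD-HC result. This stands, and it limits the point to the baseline contrast and its interpretation.

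**Healthy controls are meant to be healthy.** That is a legitimate design, but what it then measures is PD, with whatever vascular disease the patients have, against people free of vascular disease. It does not support the stronger wording in section 2.1.

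**The PD criteria do address vascular disease in part.** They exclude vascular parkinsonism and severe systemic disease and require stable vital signs. This stands, so the gap should be stated as hypertension and non-severe cardiovascular disease, not as vascular disease in general.

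**Supplementary material 3 may specify imaging covariates.** It is not shown, so their absence from the article is not held against the plan. The mismatch between the eligibility lists and the stated purpose remains either way.

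**Stronger readings that the document does not support.** A reader might infer that covariate adjustment is useless because no HC has vascular disease. Step 5 of the working shows otherwise: only the vascular effect among HCs is inestimable, and the contrast does not need it. A reader might also turn the assumed bias into a false-positive rate. For one uncorrected 5% test, 0.04-0.30 SD gives 5.3% to 22%. Those are not the plan's error rates, because section 2.9.2 uses cluster-level family-wise, FDR and Bonferroni corrections. The figure also presumes a shift in one direction, which the document does not establish for connectivity.

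**Conclusion.** The point holds for the baseline PD-HC contrast. The eligibility lists leave hypertension and non-severe cardiovascular disease possible in PD patients and impossible in HCs, and matching covers age and sex only. A difference in this contrast is therefore not by itself specific to PD.

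How much this matters cannot be read from the document. Under the assumed 20-50% prevalence and 0.2-0.6 SD shift, the bias is 0.04-0.30 SD: negligible at the low end and slightly more than one standard error at the high end.

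A reader might infer that the mismatch undermines the trial's treatment comparisons. It does not. The verum, sham and wait-list groups are randomised from one PD population under one set of criteria. The remedy is an added analysis and a change of description; no treatment analysis has to change.

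**What to change.** - Run the PD-HC contrast, at least as a prespecified sensitivity analysis, in PD patients who meet the HC cardiovascular criterion. Equivalently, keep all PD patients, add a vascular-history indicator, and report the PD coefficient.
- Record that history in a structured form at the enrollment clinical interview. Table 1 lists the interview but does not say that it covers vascular history.
- Describe the unrestricted contrast as PD versus vascular-healthy controls, and reword the claim of disease specificity in section 2.1.
- Leave the HC criteria as they are. Relaxing them part-way would produce a control group recruited under two definitions.

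**Cost.** One history item and one additional analysis, with no new scans or visits. Fewer PD patients enter the restricted contrast: with 35-55 of 69 retained (assumed), the standard error rises from 0.25 to about 0.26-0.28 SD, or by about 3-10% (0.261 / 0.254 and 0.280 / 0.254). The age and sex balance with the HCs should be rechecked in the retained patients, and the result describes PD without vascular disease, not the whole PD sample.

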### Sample size

2.3

This trial is designed as an exploratory mechanistic study, with the primary objective of detecting QNT-induced neuroplasticity using multimodal MRI. The sample size was therefore determined based on neuroimaging methodology standards. Given the lack of standardized methods for sample size estimation in acupuncture-related neuroimaging trials, we referenced fMRI studies that recommended ≥20 participants per group for robust statistical analysis (17). Accounting for a 10% attrition rate, 69 PD patients (23 per group) and 20 HCs will be enrolled. HCs undergo baseline MRI only, minimizing dropout risk. Separately, a formal power calculation for the UPDRS-III was performed using PASS 15.0. Based on our pilot data (7), the expected changes (mean ± SD) are: verum acupuncture group 14.0 ± 9.94, sham group 2.84 ± 3.08, and wait-list group 2.3 ± 3.0 (18). With α = 0.05, power = 0.90, 1:1:1 allocation, and Tukey–Kramer correction for multiple comparisons, the required sample size is 165 patients (55 per group) after adjusting for 20% dropout. This trial, however, is designed as an exploratory mechanistic study; the smaller sample of 69 patients is adequately powered for the primary neuroimaging endpoints, whereas all clinical efficacy analyses are considered exploratory and will inform the design of future large-scale multicenter trials.

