#### Neuroimaging data analysis

2.9.2

Neuroimaging data will be analyzed according to standardized pipelines, with comprehensive details provided in Supplementary material 3. For VBM, the CAT12 toolbox (SPM12, version r1720; CAT12, r1720) will be used for bias correction, tissue segmentation, and spatial normalization to MNI space. Whole-brain VBM results will be reported at cluster-level family-wise error (FWE) corrected *p* < 0.05 with an initial voxel-level threshold of *p* < 0.001. Resting-state fMRI data will be preprocessed using DPABI v6.1. Preprocessing will include discarding the first 10 volumes, slice timing correction, realignment, normalization to MNI space, spatial smoothing (6-mm FWHM), nuisance regression (Friston-24 motion parameters and WM/CSF signals), detrending, and bandpass filtering (0.01–0.08 Hz). Volumes with framewise displacement (FD) > 0.5 mm will be censored using scrubbing regressors; participants with >20% censored volumes or with maximum head motion >3.0 mm translation or 3.0° rotation will be excluded. Seed-based functional connectivity will be computed using predefined seeds from the Automated Anatomical Labeling (AAL) atlas (bilateral putamen, caudate, globus pallidus, and thalamus; seed coordinates are provided in Supplementary material 3). Voxel-wise connectivity maps (Fisher's z-transformed) will be assessed using cluster-level FWE correction (voxel *p* < 0.001; cluster *p* < 0.05). To address multiple comparisons arising from testing multiple seeds, seed-level multiplicity will be controlled using false discovery rate (FDR; Benjamini–Hochberg) across seeds (*q* < 0.05). In addition, the bilateral putamen will be designated *a priori* as the primary seed of interest, whereas results from the remaining seeds will be considered secondary/exploratory and interpreted with FDR control across seeds. DTI data will be processed using DTIStudio v3.0.3 (and the NODDI toolbox in MATLAB R2013b, if applicable). Fractional anisotropy (FA), mean diffusivity (MD), radial diffusivity (RD), and axial diffusivity (AD) will be computed. Regions of interest (substantia nigra, putamen, caudate) will be manually delineated on FA color maps by two independent raters blinded to group and time point, with inter-rater reliability assessed using intraclass correlation coefficients (ICC; ICC > 0.80 required). ROI-based statistical comparisons will apply Bonferroni correction within each predefined ROI family. SWI phase images will undergo high-pass filtering (32 × 32) before manual delineation of substantia nigra (SN) area and measurement of SN pars compacta (SNc) width. NM-MRI SNc width will be measured in the dorsoventral direction on the optimal axial slice using the ADW4.6 workstation. ICC will be assessed for all manual measurements, and the average of the two raters will be used for analysis. All statistical tests will be two-tailed with significance set at *p* < 0.05 after correction.

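### Adequate power for the imaging endpoints is asserted but not shown: the basis is a head count with no effect size, and the section uses two unexplained loss rates

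*Protocol article*

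**What the plan says.** Section 2.3 notes that acupuncture neuroimaging trials have no standard way to estimate sample size, and continues: "we referenced fMRI studies that recommended ≥20 participants per group for robust statistical analysis". It then sets the enrolment: "Accounting for a 10% attrition rate, 69 PD patients (23 per group) and 20 HCs will be enrolled". A separate, formal calculation is reported for UPDRS-III: "With α = 0.05, power = 0.90, 1:1:1 allocation, and Tukey–Kramer correction for multiple comparisons", leading to "the required sample size is 165 patients (55 per group) after adjusting for 20% dropout". The section closes by saying that "the smaller sample of 69 patients is adequately powered for the primary neuroimaging endpoints", while the clinical analyses are exploratory.

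The related passages are these:
- Section 2.6.1 makes change in multimodal MRI biomarkers the primary endpoint. It does not single out a modality or measure.
- Section 2.6.1.1 puts the primary clinical outcome, UPDRS-III change, at week 4 so that it lines up with the imaging. Table 1 and section 2.6.2 put the second MRI at week 4.
- Section 2.9.2, in the resting-state fMRI pipeline, drops participants with more than 20% censored volumes, and those whose maximum head motion exceeds set limits: "3.0 mm translation or 3.0° rotation will be excluded".

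**The concern.** Power is a property of a test against a stated effect. It needs an effect size, a measure of variability, a significance level and a defined endpoint. Section 2.3 supplies these for UPDRS-III and for no imaging measure. A recommended group size can support feasibility or convention, but it cannot by itself support a statement that the sample is adequately powered.

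What is at stake is how the primary result is read. A reader told that the imaging endpoints are adequately powered may take a non-significant result as evidence that the treatment has no effect on the brain measures. At this sample size such a result would be compatible with sizeable differences.

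The loss rates raise a second, smaller question. The same section uses 10% for one week-4 primary assessment and 20% for the other, and does not say why. The imaging target of 20 per arm is met under one rate and missed under the other.

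**Working it through.** **1. The plan's own figure.** Inputs from section 2.3: 20 per group, 10% attrition, three groups.

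20 / (1 − 0.10) = 22.2, rounded up to 23; 3 × 23 = 69. The enrolment figure reproduces exactly. The power statement cannot be reproduced, because no imaging inputs are given.

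**2. What the two loss rates imply for 23 per arm.**

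| Loss rate | Where section 2.3 uses it | Expected per arm | Target of 20 |
|---|---|---|---|
| 10% | imaging sample | 23 × 0.90 = 20.7 | met |
| 20% | UPDRS-III calculation | 23 × 0.80 = 18.4 | not met |

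The margin is 23 − 20 = 3 losses per arm, or 3/23 = 13.0%. At 20% loss, an expected 20 per arm would need 20/0.80 = 25 per arm, or 75 in total. For resting-state fMRI, participants excluded for motion under section 2.9.2 come out of the same margin of three. No expected exclusion rate is given, so the size of that extra loss is unknown.

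**3. Detectable difference.** The documents give no imaging effect size, so I solved for it. The assumptions are mine: a two-sample t-test of change between two arms, two-sided alpha, equal variances, and d in units of the standard deviation of the measure. With n per arm, power = P(T > t_crit), where T is noncentral t with 2n − 2 degrees of freedom and noncentrality d × √(n/2). For n = 20, alpha 0.05: df = 38, t_crit = 2.024, and power reaches 0.80 at d = 0.91.

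| n per arm | d for 80% power, one contrast at 0.05 | d for 80% power, alpha 0.05/3 | Power at d = 0.5 (alpha 0.05) | Power at d = 0.8 (alpha 0.05) |
|---|---|---|---|---|
| 18 | 0.96 | 1.13 | 0.31 | 0.65 |
| 20 | 0.91 | 1.06 | 0.34 | 0.69 |
| 23 (no loss) | 0.84 | 0.99 | 0.38 | 0.76 |

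The alpha 0.05/3 column is an illustration only. It assumes Bonferroni correction over the three pairwise group contrasts, which the article does not state for imaging. Section 2.9.2 does specify cluster-level family-wise error control, FDR across seeds and Bonferroni within ROI families. Any such correction makes the detectable difference larger than in the single-contrast column.

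**4. Is there one primary measure to which the claim could apply?** Section 2.9.2 names the bilateral putamen as the primary seed, but only within the connectivity analysis, which is voxel-wise. Nothing ranks connectivity above grey matter volume, diffusion, SWI or neuromelanin measures. The power statement therefore has no single defined target.

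**The case against.** The strongest reply is that the section is open about its basis. It says no standard method exists, cites the group-size recommendation and calls the trial an exploratory mechanistic study. A reader can see in the same paragraph where 69 comes from. That is fair as a defence of the sample size, and I do not argue that 69 is wrong for an exploratory study. It does not defend the power statement, which sits in the same sentence as the exploratory label and claims more than the basis can give.

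On the loss rates, the 20% belongs to a separate calculation for 165 patients who are not being enrolled, and UPDRS-III is also followed to week 8, whereas MRI ends at week 4. On its own 10%, the plan meets its target. This stands. What remains is that both primary assessments are at week 4 and the difference is not explained. The practical effect is also small: going from 20 to 18 per arm moves the detectable d from 0.91 to 0.96.

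Four stronger readings are tempting and are not supported:
- A reader might infer that the target of 20 will be missed. The documents show only that it would be missed on average at 20% loss.
- A reader might compute the chance that at least one arm falls below 20. The plan sets no such minimum for every arm; ordinary inflation aims at the expected number.
- A reader might compute power at alpha 0.001. In section 2.9.2 that value is the threshold for forming clusters; inference is at cluster-level 0.05.
- A reader might apply the motion rule to all imaging. It is stated only for resting-state fMRI, and section 2.6.2 schedules scans in the ON medication state partly to limit motion.

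Whether d = 0.91 is implausibly large cannot be judged from the article, since no variability is given for any MRI measure.

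**Conclusion.** The point holds in a limited form. The statement of adequate power for the primary imaging endpoints is unsupported: it has no effect size, variability, alpha or power behind it, and no single primary measure to which it applies. Under the assumptions above, 80% power for one uncorrected pairwise contrast needs d of about 0.91 with 20 per arm, and about 0.84 even if nobody is lost. Power at an assumed d of 0.5 is about one in three.

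The two loss rates are an unexplained inconsistency that needs reconciling, but they do not prove that the target fails. The margin is three losses per arm from all causes.

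The article nowhere says that a null imaging result will be read as absence of effect. That is a risk created by the wording, not a stated intention.

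**What to change.** In section 2.3:
- Delete the claim of adequate power and say that no power calculation was made for the imaging endpoint.
- Give the detectable standardized difference for one two-sided 0.05 pairwise contrast at 80% power: about 0.91 with 20 per arm and 0.96 with 18. Add that correction across contrasts, seeds, regions or modalities raises it; for example, to about 1.06 with 20 per arm if three contrasts were Bonferroni-corrected, labelled as an assumption.
- Use one justified loss rate in both calculations, or explain why they differ. State the expected number per arm, and for resting-state fMRI include unusable scans.

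In section 2.9.2, say that non-significant imaging results will be reported with confidence intervals for ROI and other scalar measures, and will not be presented as absence of effect.

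The cost is text only. The stated figure becomes less favourable, and no patients are added.
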